### Statistical Analysis

The distribution of socio-demographic and clinical characteristics between groups in the baseline state will be summarized using descriptive statistics. The change in clinical and functional variables with regard to baseline evaluation at strategic points of the intervention will be analyzed using mixed-effects repeated-measures linear models, including as fixed factors time, treatment conditions and their interactions, and as a random factor the site. The differences between groups, for the categorical variables and main clinics, will be analyzed by adding covariates to the models. Those covariates that are statistically significant may be added in the same model to determine which covariates are best predictors of the response. The size of the effects will be estimated using the g of Hedges or the r of Pearson. It will be corrected for multiple comparisons. The statistical software used for the analysis will be the latest available version of R. We will conduct an intention to treat (ITT) analysis. The “Last Observation Carried Forward” (LOCF) method will be used for losses of follow-up.

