### Study Outcomes

The primary outcome is to test the efficacy of EMDR therapy in reducing the severity of substance use in patients with comorbid SUD and a history of psychological trauma, irrespective of whether the patient meets DSM-V PTSD criteria. Changes from baseline in the severity of substance use are measured by the Timeline Follow Back (TLFB) (31), the Severity of Dependence Scale (SDS) (32), and the Visual Analog Scale (VAS).

The secondary outcome is to test the efficacy of EMDR in improving trauma-related psychological symptoms, psychopathological symptoms, and the overall functionality in SUD patients with a history of psychological trauma. Changes in psychological trauma and dissociative symptoms are measured using the Global Assessment of Posttraumatic Stress Questionnaire (EGEP-5) (33), the Impact of Event Scale-Revised (IES-R) (34), and the Dissociative Experiences Scale (DES) (35), respectively. The type and severity of traumatic experiences are measured using the Childhood Trauma Questionnaire (CTQ) (36) and The Holmes-Rahe Life Stress Inventory (37). Changes in psychopathological symptoms are measured by the Hamilton Depression Rating Scale (HDRS) (38), Young Mania Rating Scale (YMRS) (39), and the Brief Psychiatric Rating Scale (BPRS) (40). Changes in overall functioning will be measured using the Functioning Assessment Short Test (FAST) (41).

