In this trial, all patients meeting the inclusion criteria will receive the baseline (T0) assessment. After T0, participants will be assigned to the EMDR or TAU group following a biased coin procedure (46): (1) the first two patients will be randomly allocated to EMDR with *p* = 0.5, (2) the next patient will be allocated as follows: (b1) if one group already includes at least two more patients than the other group, the patient will be randomly allocated to EMDR with *p* = 0.8 is this is the smallest group and with *p* = 0.2 if it is the largest group, (b2) otherwise, we will first simulate that the patient is allocated to EMDR and calculate the sum of the between-group square standardized differences in site, age, sex, diagnosis (dual vs. not dual) and number of substances consumed during the month before the randomization (none. one or more than one), we will then simulate that the patient is allocated to TAU and recalculate the sum, and finally randomly allocate the patient to EMDR with *p* = 0.8 if this was associated to the smallest sum and with *p* = 0.2 if not. For example, if we had already included 10 patients to the EMDR group and 8 patients to the TAU group, the 19th patient would be randomly allocated with *p* = 0.2 for EMDR and *p* = 0.8 for TAU. If he/she was allocated to TAU, for the 20th patient we would calculate the above sum of covariates after simulating that the he/she is allocated to EMDR and after simulating that he/she is allocated to TAU, and if the sum of the EMDR simulation was larger than the sum of the TAU simulation, we would randomly allocate the 20th patient with *p* = 0.2 for EMDR and *p* = 0.8 for TAU. Following this procedure, the final groups should be balanced in size and matched in site, age, sex and diagnosis. All steps of the randomization process will be automatically carried out by an independent researcher in a central location using a computer program.

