### Computation of Sample Size

The study aims to assess the efficacy of EMDR therapy compared with TAU, in inpatients with SUD, in terms of a reduction in substance use, a reduction in symptoms associated with craving and associated symptoms of anxiety and depression, and an improvement in functioning.

We aim for the study to be able to detect medium-sized differences in the pre-post changes between groups with an 80% statistical power. Given that there are no previous studies that report the variability of these changes, we have defined medium-sized differences as those with a medium effect size (*d* = 0.5). With the function power.t.test from R (http://www.r-project.org/), we have calculated that the number of patients required to detect medium-sized differences (*d* = 0.5) with a statistical power of 80% is *n* = 64 per intervention group (two groups, total *n* = 128). Assuming a loss percentage of approximately 10% of the patients in the study, it would be necessary to recruit approximately 142 patients, 71 for each intervention branch.

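### The change-from-baseline model names no baseline value of the outcome, so the trial gives up precision that its T0 data could supply at no cost

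*Protocol article*

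**What the plan says.** All the relevant statements are in the Methods of the protocol article.

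- **Outcome form** (Study Outcomes): "Changes from baseline in the severity of substance use are measured by the Timeline Follow Back (TLFB"), together with the SDS and the VAS.
- **Analysed quantity** (Statistical Analysis): "The change in clinical and functional variables with regard to baseline evaluation at strategic points of the intervention will be analyzed" by mixed-effects repeated-measures linear models.
- **Model terms** (same section): "including as fixed factors time, treatment conditions and their interactions, and as a random factor the site". The outcome's own baseline value is not listed.
- **Covariates** (same section): group differences "will be analyzed by adding covariates to the models", and then "Those covariates that are statistically significant may be added in the same model to determine which covariates are best predictors of the response". No covariate is named.
- **Sizing** (Computation of Sample Size): the aim is to "detect medium-sized differences in the pre-post changes between groups", and "we have defined medium-sized differences as those with a medium effect size", d = 0.5.
- **Baseline data** (Randomization Procedure): "all patients meeting the inclusion criteria will receive the baseline (T0) assessment", and allocation follows it. Tables 2 to 4 show a T0 value for the TLFB, SDS and VAS and for every secondary scale that is measured again later.

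**The concern.** A change score subtracts the whole baseline value, and with it all the baseline noise. Unless baseline and follow-up are very highly correlated, that is more than the follow-up value warrants. The change score also stays negatively correlated with baseline. An arm that happens to start higher will tend to show a larger fall, and part of that fall is regression to the mean. Using baseline as a covariate lets the data set the weight, which removes this dependence and usually lowers the variance.

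Precision and protection against a chance difference at entry are at stake, on outcomes where patients may differ widely at entry. Allocation balances site, age, sex, dual diagnosis and number of substances used in the previous month. It does not balance the TLFB, SDS or VAS scores themselves.

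**Working it through.** **1. The plan's own figure.** Inputs from Computation of Sample Size: d = 0.5 on the pre-post change, 80% power, two equal groups, power.t.test. Alpha is not stated; I take its default, two-sided 0.05. The solution is 63.77, so 64 per arm, as stated. Power at 64 per arm is 80%. The unadjusted change-score comparison is therefore sized consistently.

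**2. Does the listed model adjust for baseline implicitly?** There are two readings.

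- *Change is the response.* The treatment contrast at a visit is the difference in mean change.
- *T0 is kept as one of the repeated responses.* The contrast is the treatment-by-time interaction. In a simulated data set with 64 per arm, five sites and no missing values (LOCF would also leave none), the T2 interaction was 0.0611 with a patient random effect and 0.0611 with a site random effect. The raw difference in mean change was also 0.0611.

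Neither reading adjusts for baseline.

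**3. Size of the loss, equal SDs.** Let s be the common SD at baseline and follow-up and ρ their correlation. The article gives neither, so ρ = 0.3 to 0.7 is assumed.

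- Var(change) = 2(1 − ρ)s²
- Var(adjusted) = (1 − ρ²)s²
- Ratio = (1 + ρ)/2, so the variance saving is (1 − ρ)/2 and the standard-error saving is 1 − √[(1 + ρ)/2]

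If d = 0.5 is on the change-score SD, the adjusted analysis behaves like d = 0.5/√[(1 + ρ)/2].

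| ρ | Var(change)/s² | Var(adjusted)/s² | Variance saving | SE saving | Equivalent d | Power, 64 per arm | n per arm for 80% |
|---|---|---|---|---|---|---|---|
| 0.3 | 1.40 | 0.91 | 35% | 19% | 0.620 | 94% | 42 |
| 0.5 | 1.00 | 0.75 | 25% | 13% | 0.577 | 90% | 49 |
| 0.7 | 0.60 | 0.51 | 15% | 8% | 0.542 | 86% | 55 |

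A simulation of 8,000 trials at each ρ, 64 per arm, gave variance savings of 35%, 24% and 14%. Outside this range the saving is 50% at ρ = 0 and 5% at ρ = 0.9.

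**4. Unequal SDs.** Let the follow-up SD be k times the baseline SD s. Then Var(change) = (1 + k² − 2ρk)s² and Var(adjusted) = k²(1 − ρ²)s². The values of k are illustrations.

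| ρ | k = 1.3 | k = 0.7 |
|---|---|---|
| 0.3 | 1 − 1.538/1.910 = 19% | 1 − 0.446/1.070 = 58% |
| 0.5 | 1 − 1.268/1.390 = 9% | 1 − 0.368/0.790 = 53% |
| 0.7 | 1 − 0.862/0.870 = 1% | 1 − 0.250/0.510 = 51% |

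The saving is never negative in these formulas, but its size depends on quantities that the article does not report.

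**5. Chance imbalance.** With equal SDs, an observed baseline difference Δ moves the expected change-score estimate by −(1 − ρ)Δ. Under simple randomisation with 64 per arm, the standard error of Δ is √(2/64) = 0.177 s. At ρ = 0.5 a one-standard-error imbalance moves the estimate by 0.5 × 0.177 = 0.088 s. The planned effect on that scale is 0.5 × √[2(1 − 0.5)] s = 0.5 s, so the shift is about 18% of it. The biased coin may make such imbalance smaller than this to the extent that its factors predict the scores.

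**The case against.** The strongest objection is that this is an omission in a condensed article, and that baseline adjustment is something an analysis plan would settle. The covariate clause leaves room for it. That argument would hold if the article were silent on the model, but it fixes both the analysed quantity and the terms. The clause that might have supplied a baseline term chooses covariates by significance in order to find predictors of response, which is not pre-specified adjustment of the treatment effect. What stands is that a baseline term is not excluded. A reader might infer that the plan rules out adjustment, and the text does not say so.

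The second objection is that nothing here is invalid, and this also stands. Under randomisation the unadjusted comparison of changes is unbiased, the sizing and the analysis use the same quantity, and 64 per arm gives the stated power. A reader might infer bias or an underpowered trial; the article's figures support neither. If intention to treat with LOCF keeps all 71 per arm, power at the same d would be about 84%, before any effect of LOCF on d.

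Third, the allocation balances number of substances used in three classes, which is related to the primary outcome. That reduces the exposure to imbalance, but it does not take baseline variance out of the change score.

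A reader might also offset the gain against the promised multiplicity correction. The article names no correction method, so that is a separate question and adds no weight here.

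**Conclusion.** The point holds as a free improvement, not as an error. The stated model gives an unadjusted change-score comparison on either reading of the repeated-measures structure, and nothing in the text commits to a baseline term.

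The cost is efficiency and exposure to chance imbalance in the baseline scores. At an assumed correlation of 0.3 to 0.7 with equal SDs, the loss is 35% to 15% of the variance. It is tempting to read that as a known waste, but the article gives no SD and no correlation, and it says that no earlier study reports the variability of these changes. The figure also describes variance: interval widths would shrink by only 19% to 8%. With a follow-up SD 1.3 times the baseline SD the saving could be as low as 1%; with 0.7 times it exceeds 50%.

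**What to change.** For each outcome measured at T0, pre-specify a model of the post-baseline visits (T1, T2 and T3 for the substance-use measures; T2 and T3 for the others). Include treatment, visit, their interaction, that outcome's T0 value and the interaction of the T0 value with visit. A constrained longitudinal model, with T0 as a response and a common baseline mean in both arms, is an equally good choice. Report the adjusted difference between arms at T2 and at T3. State that the baseline term enters whatever its p-value, and keep the significance-based search for predictors as a separate, exploratory step.

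The number of relapses, named in the Hypotheses, has no T0 value described and falls outside this change.

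The cost is a sentence or two in the analysis section. It needs no new data, visits or patients, and the sample size can stay as it is.

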**ASSESSMENTS**					
FAST	X			X	X

*PRISM, Psychiatric Research Interview for Substance and Mental Disorders; MINI, Mini-International Neuropsychiatric Interview; HDRS, Hamilton Depression Rating Scale; YMRS, Young's scale for the evaluation of the Mania; BPRS, Brief Scale of Psychiatric Evaluation; TLFB, Timeline Followback; SDS, Dependence severity scale; EVA, Analog visual scale; CTQ, Childhood Trauma Questionnaire; H-RLSI, The Holmes-Rahe Life Stress Inventory; EGEP, Global Assessment of Posttraumatic Stress Questionnaire; IES-R, Scale of the impact of events reviewed; DES, Scale of Dissociative Experiences; EMDR, Eye movement desensitization and reprocessing therapy; TAU, Treatment as usual; FAST, Functioning Assessment Short Test*.

The study has been approved by the Ethic Committees of the Hospital Benito Menni, Germanes Hospitalàries del Sagrat Cor de Jesús (PR-2018-04), and the IMIM, Parc de Salut Mar (2017/7615/I). All participants will sign informed consent prior to enrollment. Details of the trial design can be also gathered from Supplementary Material (Standard Protocol Items: Recommendations for Interventional Trials [SPIRIT] Checklist).

This is a multicenter phase II collaborative project will involve the participation of five different centers from the Barcelona catchment area, Spain: four outpatient addiction clinics pertaining to the Institute of Neuropsychiatry and Addictions (INAD), Parc de Salut Mar, and a fifth pertaining to the Hospital Benito Menni, in Sant Boi de Llobregat. Both institutions involved are centers of reference in mental health treatment and research, facilitating the recruitment and development of the project. EMDR therapists have extensive experience in EMDR protocols and SUD. All participating raters will be trained in the blind-to-treatment application of all clinical assessments.

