## Stepwise Procedures

### Intervention

#### EMDR

Patients in the EMDR condition will receive 20 individual sessions of 60 min each, using the standard EMDR therapy protocol developed by Shapiro (47) and a further specific protocol for SUD, the CRAVEX protocol, developed by Hase (48) to treat both trauma-related symptoms and SUD symptoms, respectively.

The current standard protocol includes eight phases, briefly described below:

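### The stated model has no term for EMDR therapist, a layer of clustering in the EMDR arm only, so precision is overstated if therapists differ in outcome

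*Protocol article*

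**What the plan says.** The Statistical Analysis section of the protocol article gives the model as mixed-effects repeated-measures, "including as fixed factors time, treatment conditions and their interactions, and as a random factor the site". It names no therapist term and no random effect specific to one arm.

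The design that this model has to describe is set out elsewhere in the article:

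- **Centres and therapists.** Methods (text after Table 1) places the trial in "five different centers from the Barcelona catchment area, Spain" and states that "EMDR therapists have extensive experience in EMDR protocols and SUD". It gives neither the number of therapists nor their caseloads.
- **EMDR arm.** Under Intervention, EMDR: "Patients in the EMDR condition will receive 20 individual sessions of 60 min each". Methods describes this as TAU plus EMDR, against TAU only.
- **TAU.** Under Intervention, TAU, patients in both arms receive the unit's standard care. This may include visits to a psychologist using CBT that is not trauma-focused.
- **Sample size.** Computation of Sample Size aims at a standardised difference of 0.5 "with an 80% statistical power", calculated "With the function power.t.test from R". The result is 64 per group, raised to 71 per group for about 10% loss. There is no design effect.

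**The concern.** With 71 EMDR patients at 20 one-hour sessions each, the arm needs up to 71 × 20 = 1,420 therapist hours. That patients share therapists is therefore an inference, but a practically certain one. Patients of one therapist may have outcomes more alike than patients of different therapists. The EMDR section leaves the therapist some judgement, for instance over the treatment plan and the choice of the next target memory.

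This layer exists in one arm only. A random site intercept moves both arms of a site by the same amount. Because allocation balances site between arms, it largely cancels from the treatment contrast. Variation among EMDR therapists does not cancel. With one therapist per site it becomes a site-by-treatment effect, for which the model has no term. The model then treats EMDR patients of the same therapist as independent given site.

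At stake is the stated precision of every treatment comparison. A chance run of good or poor results with a few therapists would be reported with more certainty than it deserves.

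**Working it through.** **The plan's own figure.** For d = 0.5, two-sided 5% and 80% power, the exact two-sample t calculation gives 64 per group (power 80.15%; 63 gives 79.5%). The article states no alpha; two-sided 0.05 is the default of the R function and reproduces 64. For losses, 128/0.9 = 142.2, in line with the stated 142. The plan's figure therefore reproduces, under independent patients.

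**Inputs.** From the article: 64 analysed per arm, d = 0.5, five centres, site as the only random factor. Assumed, because not given: k EMDR therapists with equal caseloads m = 64/k, and a therapist ICC within the EMDR arm. Total variance is set to 1 in both arms.

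**Formulas.**

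- Design effect in the EMDR arm: DE = 1 + (m − 1) × ICC
- Variance of the contrast: true (DE + 1)/64; assumed by the model 2/64
- Ratio of true to reported standard error: R = √((DE + 1)/2)
- Actual type I error: 2 × (1 − Φ(1.96/R))

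**Middle case, k = 5 and ICC 0.05.** m = 64/5 = 12.8; DE = 1 + 11.8 × 0.05 = 1.59; R = √(2.59/2) = 1.138; type I error = 2 × (1 − Φ(1.722)) = 8.5%.

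| k | ICC | DE | R | Type I error |
|---|---|---|---|---|
| 4 | 0.02 | 1.30 | 1.07 | 6.8% |
| 4 | 0.10 | 2.50 | 1.32 | 13.8% |
| 5 | 0.05 | 1.59 | 1.14 | 8.5% |
| 10 | 0.02 | 1.11 | 1.03 | 5.6% |
| 10 | 0.05 | 1.27 | 1.07 | 6.6% |
| 10 | 0.10 | 1.54 | 1.13 | 8.2% |

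R from 1.03 to 1.32 means that the true standard error is 3% to 32% above the reported one. Put the other way, the reported one is 1 − 1/1.027 = 3% to 1 − 1/1.323 = 24% too small. At ICC 0, R = 1 and nothing is lost.

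**Does the site term help?** A simulation (6,000 runs per setting, 5 sites, 64 per arm, site ICC 0.02) analysed one change score per patient. Fixed site effects stood in for the random intercept.

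| Therapist ICC | Type I error, one therapist per site | Type I error, two per site |
|---|---|---|
| 0 | 5.3% | 4.6% |
| 0.02 | 7.0% | 5.5% |
| 0.05 | 8.3% | 6.9% |
| 0.10 | 12.7% | 8.3% |

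With one therapist per site and ICC 0.05, the estimate had a true standard deviation of 0.201 against a mean model standard error of 0.175. The common site effect does not remove the therapist variance. The mean estimate stayed at about 0 in every setting, so there is no systematic bias.

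**Power once the standard error is right, k = 5 and ICC 0.05.** True SE = √(2.59/64) = 0.201. With z: Φ(0.5/0.201 − 1.96) = 70%. With Satterthwaite degrees of freedom (10.4), about 62%. The plan aims at 80%.

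**The case against.** The strongest objection is that the model sentence is a summary. It also names no patient effect or within-patient covariance, which a repeated-measures model needs, so the list of random terms is evidently incomplete. A full analysis plan may contain a therapist term, and the article does not say that the therapist goes unrecorded. This lowers confidence but does not remove the point: the article does fix a between-patient clustering factor, site, and that factor does not match the clustering that the design creates.

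Second, the harm is conditional. Therapists are experienced and follow a standard eight-phase protocol, which may keep differences small. With 10 therapists and ICC 0.02, type I error is only 5.6%. This stands.

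A reader might also infer stronger things that the documents do not support:

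- **That TAU-only patients share no clinicians.** The TAU section lets them share unit staff, including psychologists. But TAU is given in both arms, so the asymmetry is only the added EMDR layer.
- **That therapist differences bias the EMDR effect.** They do not, on average. They add variance that the model does not count.
- **That the therapist decides the mix of standard and CRAVEX sessions.** The EMDR section says that both are applied, not who decides the mix. For the modality of stimulation, the stated ground for switching is tolerability to the patient.

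**Conclusion.** The point holds as a conditional fault of precision. The stated random structure omits therapist clustering that exists in the EMDR arm only, and a site effect common to both arms does not replace it. If the therapist ICC is above 0, confidence intervals are too narrow and the nominal 5% is exceeded.

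The size cannot be fixed from the documents. The range given in the working rests on assumed therapist numbers and ICCs, equal caseloads and a single change score, so it indicates scale and is not an estimate for this trial. The 64 analysed per arm is the plan's own basis. If all 71 per arm entered the intention-to-treat analysis, caseloads would be larger and the middle case slightly worse: m = 71/5 = 14.2, DE = 1 + 13.2 × 0.05 = 1.66, R = √(2.66/2) = 1.153, type I error 8.9%.

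The change is worth making, but nothing here shows that the trial's conclusion would be wrong.

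**What to change.** 1. Record the treating EMDR therapist for every EMDR patient, during treatment.
2. Keep site in the model and add a random therapist effect in the EMDR arm only, set to zero for TAU only (a partially nested model). If each site has one EMDR therapist, use a random site-by-treatment effect instead.
3. Use Satterthwaite or Kenward-Roger degrees of freedom.
4. If therapists are too few to estimate their variance, report this model as a sensitivity analysis beside the site-only model, and word the conclusion on EMDR accordingly.

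The cost in data is one field, and in text a few sentences. The statistical cost is wider confidence intervals and an imprecisely estimated therapist variance. Power also falls, to about 70% or 62% in the middle case above. That should be stated openly as a limit of the design. It is not a reason to enrol more patients.

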## Methods

This is a multicenter phase II rater-blinded randomized controlled trial, phase II, with two parallel branches, EMDR and TAU, of patients diagnosed with SUD who have a comorbid history of psychological trauma, even if they do not currently meet DSM-V criteria for PTSD. The patients will be matched by site, age, sex, and diagnosis. One group will consist of TAU plus 20 individual 60-min EMDR sessions over a duration of 6 months, while the other group will receive TAU only. Patients will be evaluated at baseline (T0), 3 months (T1: only substance use-related symptoms), post-treatment at 6 months (T2), and at 12 months as follow-up (T3) (see Table 1). Clinical raters carrying out evaluations will be blind to the participants' research condition. Patients will not be blind to treatment as a sham alternative to EMDR therapy is impossible due to its use of bilateral stimulation.

**Table 1 T1:** SPIRIT flow diagram: schedule of enrolment, interventions, and assessments.

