## Limitations

A limitation of this study is the inclusion of heterogeneous patients with various psychiatric diagnoses, including SUD with somatic and other psychiatric comorbidities. This trial has been specifically designed as a pragmatic real-world study with few exclusion criteria. We believe this limitation can be sufficiently controlled by matching samples in both arms and by the fact that the main common clinical underlying variable of all patients is a comorbid psychological trauma. Furthermore, the lack of control regarding drug treatment is a potential source of bias. To partly overcome this limitation, the “pharmacological treatment” variable will be taken into account and the treatment regimen should not be changed as far as possible, once patients have been stabilized. Moreover, it should be noted that our center has extensive experience in the treatment of SUD and uses standardized treatment protocols, which will also help limit this potential issue.

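### Allocation balances five factors, but the stated model names only site and does not say which model gives the treatment effect; if the other four predict change, the analysis is conservative

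*Protocol article*

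**What the plan says.** The Randomization Procedure section of the Protocol article computes, for each possible assignment of the next patient, a sum of "between-group square standardized differences in site, age, sex, diagnosis (dual vs. not dual) and number of substances consumed during the month before the randomization". It will then "randomly allocate the patient to EMDR with *p* = 0.8 if this was associated to the smallest sum and with *p* = 0.2 if not". When one arm leads by two or more patients, the coin follows arm size alone and ignores the covariates.

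The Methods section gives a shorter list: "The patients will be matched by site, age, sex, and diagnosis". It leaves out number of substances, which the algorithm does balance.

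The Statistical Analysis section describes mixed-effects repeated-measures models "including as fixed factors time, treatment conditions and their interactions, and as a random factor the site". Two sentences on covariates follow. The first is unconditional but names no covariate: "The differences between groups, for the categorical variables and main clinics, will be analyzed by adding covariates to the models". The second is optional and turns on significance: "Those covariates that are statistically significant may be added in the same model to determine which covariates are best predictors of the response". Neither says that age, sex, diagnosis and number of substances enter the treatment comparison, and neither identifies the model from which the treatment effect will be reported.

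**The concern.** Balancing a prognostic factor by design reduces the true sampling variance of the treatment difference. A model that omits the factor does not see this reduction. It leaves the factor's contribution in the residual and reports a standard error suited to complete randomisation. Intervals are then too wide, the test rejects too rarely under the null, and the precision gained by the allocation scheme is not used. The trial has only 80% planned power, so the loss matters if these factors are as prognostic as their choice for balancing implies.

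There is also a question of specification. The section leaves open a site-only model, a model with some covariates, and a model with the significant ones combined. Each can give a different estimate of the treatment effect.

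**Working it through.** **Inputs from the Protocol article.** Five allocation factors and a 0.8/0.2 coin (Randomization Procedure); model terms (Statistical Analysis); d = 0.5, 80% power, 64 per arm, about 10% loss (Computation of Sample Size). Not stated: alpha, taken as two-sided 0.05, and the share of variance in the change explained by the four unnamed factors (R²), taken over a range.

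**The plan's own figure.** A two-sample t-test with d = 0.5 and 80% power gives n = 63.77, so 64 per arm; power at 64 is 0.801. Then 128/0.9 = 142.2 and 64/0.9 = 71.1. The plan's 142 and 71 are reproduced, and this point does not affect them.

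**Mechanism.** With outcome SD 1 and N = 128, a model without the factors reports an SE near 2/√128 = 0.177 whatever R² is. Under perfect balance the true SE would be 0.177·√(1 − R²). The reported SE would then be too large by 1/√(1 − R²), which is 1.05, 1.12 and 1.20 at R² = 0.1, 0.2 and 0.3. Type I error would be 2·P(Z > 1.96/√(1 − R²)) = 3.9%, 2.8% and 1.9%. These are limiting values, because a 0.8 coin does not reach perfect balance.

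**Simulation of the stated coin.** 4000 trials, N = 128, one post-baseline comparison. Assumed: five equal sites, normal age, sex 30/70, dual diagnosis 50/50, substances 30/40/30, and the four non-site factors equally prognostic. Site was entered as fixed.

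| R² | Site-only: mean SE | True SD | Ratio | Type I | Power, site-only | Power, all five |
|---|---|---|---|---|---|---|
| 0 | 0.177 | 0.177 | 1.00 | 5.0% | 0.79 | 0.79 |
| 0.1 | 0.177 | 0.170 | 1.04 | 4.1% | 0.80 | 0.83 |
| 0.2 | 0.177 | 0.163 | 1.09 | 3.2% | 0.81 | 0.87 |
| 0.3 | 0.177 | 0.155 | 1.14 | 2.5% | 0.82 | 0.91 |

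With all five factors in the model, type I error was 5.0% in every row, and SE and SD agreed (both 0.159 at R² = 0.2). The Monte Carlo error on a 5% rate is √(0.05 × 0.95/4000) = 0.34 percentage points. A second simulation of the coin at 64 per arm gave site-only type I error of about 4.8%, 3.7% and 2.7% and power of 0.79, 0.81 and 0.82, against 0.82, 0.87 and 0.91 adjusted. The ranges quoted in the conclusion cover both.

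**Control.** Under complete randomisation the site-only model was correct (at R² = 0.2, SE 0.179, SD 0.179, type I error 4.9%). The discrepancy therefore comes from balancing without adjusting.

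**Selection by significance.** Keeping only covariates with p < 0.05 gave type I error of 4.8% to 5.2% and power of 0.82, 0.86 and 0.91 at R² = 0.1, 0.2 and 0.3. Taking the smallest p-value of the three models gave 5.2% to 5.5%.

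**How the factors must enter.** If baseline is one of the repeated responses, the treatment-by-time contrast compares within-patient changes. A covariate with the same coefficient at every visit cancels from each patient's change. In one simulated dataset (128 patients, three visits, patient random intercept), the contrast was −0.697 with SE 0.195 both without and with main-effect covariates. The SE fell to 0.180 only with covariate-by-time terms. If the response is a change or post-baseline score, main effects are enough.

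**The case against.** The strongest defence is textual. Covariates are to be added without condition; significance governs only a later, optional joint model whose stated purpose is to find predictors of response. That reading is fair, and it stands: the document does not make significance the entry rule for the treatment estimate. A separate analysis plan could also name the covariates, which would settle the matter. But the article itself states the allocation factors, the model terms and a covariate rule. As stated, these do not fit together, and no sentence ties the treatment effect to one model.

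The losses above also belong to a site-only analysis. If covariates were in fact selected by significance, strong ones would usually be kept: about 80% of the time each at R² = 0.2 and 96% at R² = 0.3. Error rates and power would then be close to those of full adjustment. This stands too.

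Three stronger readings are tempting and not supported:

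- A reader might infer that selecting covariates by p-value materially distorts the error rate. In the simulation it did not.
- A reader might take the perfect-balance figures (SE 5%, 12% and 20% too large) as the size of the problem. The coin is probabilistic and sometimes ignores the covariates, so they overstate it.
- The Limitations section says that the pharmacological treatment "variable will be taken into account and the treatment regimen should not be changed as far as possible", and the TAU section allows medication to be readjusted. A reader might infer that medication after randomisation will be a model covariate and absorb part of the effect. The document does not say so.

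**Conclusion.** The mismatch between allocation and stated model is real, and it acts in the conservative direction. If the site-only model supplies the treatment effect, and the four other factors explain 10%, 20% or 30% of the variance in change:

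- the SE is about 2–4%, 9% or 14% too large;
- type I error is about 4–5%, 3–4% or 2.5% instead of 5%;
- about 3, 6 or 9 percentage points of power are forgone (0.83 − 0.80, 0.87 − 0.81, 0.91 − 0.82).

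Nothing is lost if the factors do not predict change. The size rests on an assumed R², since the document reports that the variability of these changes is unknown, and on the assumed covariate distributions. The open choice of model is a prespecification gap with little numerical effect on error rates. The point does not threaten the trial's validity, but correcting it costs little.

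**What to change.** State in the Statistical Analysis section that the treatment-effect model for every outcome includes site, age, sex, dual diagnosis and number-of-substances category, whatever their significance. Enter them as covariates when change or the post-baseline score is the response. Enter them with covariate-by-time terms when baseline is part of the repeated-measures response; a site effect that is constant over visits cancels in the same way, so site then needs its own time term.

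Label the significance-based step as an exploratory predictor analysis that does not feed the treatment estimate. Use the same five-factor list wherever matching is described.

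The cost is a few sentences. All five variables are already needed for allocation. Beyond site, the factors use 1 + 1 + 1 + 2 = 5 coefficients. Covariate-by-time terms add 5 × 3 = 15 for the substance-use measures (three post-baseline visits) or 5 × 2 = 10 for the others; fixed site-by-time terms for five centres add 4 per visit. This is affordable with 142 patients, and the sample size stays as it is.
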